### Specific case descriptions

The quantitative analyses described above are designed to measure EM added value when used in Do-Confirm mode. Yet EMs are arguably designed to be used in Read-Do or Sampling mode in the setting of a true crisis. EM use may also have unforeseen impacts on patient care and team dynamics that warrant prompt remedying. Resuscitations team personnel are encouraged to request prompt contact—via the digital EM—with the research team to report events or concerns relating to EM use during specific situations. The following information is extracted from a structured interview with the personnel regarding the report (online supplemental appendix A):

10.1136/bmjopen-2022-071545.supp1Supplementary data

Patient age, sex, presenting complaint and suspected diagnosisSeniority of the physician initially in charge of the caseEvents or concerns relating to EM useMode of EM use (Do-Confirm, Read-Do, Sampling) and sections relevant to the casePersonnel’s assessment of the impact of the EM on patient carePersonnel’s assessment of impact of the EM on team members and teamworkPersonnel’s suggestions for EM improvement

### Data analysis

Descriptive statistics are used to analyse EM use data and determine the following (average over and trends throughout the pilot study period):

Frequency of EM use and mode of use (Do-Confirm, Read-Do or Sampling)Which checklists or fact sheets are most frequently accessedTime between login to and logout from the digital EMSubjective degree of EM value and correlation with specific checklists or fact sheets

Descriptive statistics are also used to determine whether EM use is associated with length of stay in the RR, length of hospital admission and mortality. These analyses are hypothesis-generating and not intended to infer causality. For the 150 patients that are externally reviewed, descriptive statistics are used to report the proportions of interventions deemed indicated, of neutral value or not indicated.

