## Methods and analysis

### Setting, patient population and personnel

The study will be carried out in the resuscitation room of the ED of Skåne’s University Hospital at Lund (referred to hereafter as Lund’s RR). Lund’s RR is designed for the simultaneous management of three priority 1 patients. EM access during clinical practice will be provided in September 2023. The study population consists of consecutive priority 1 patients managed in the Lund’s RR during the 6-month period prior to, and the 6-month pilot study period following EM implementation. Patients are deemed to be priority 1 based on vital signs and symptoms according to the Rapid Emergency Triage and Treatment System (http://predicare.se/) the most commonly used triage system in Sweden. The yearly number of priority 1 patients treated in Lund’s RR is roughly 4000 and consists of adult patients (>18 years) with medical or surgical emergencies and patients of all ages with level 1 trauma. Most of these patients are brought to the RR via ambulance, and only occasionally are they identified at the triage or at later stage of ED care. All priority 1 patients are managed immediately in the RR by multidisciplinary resuscitation teams. The core resuscitation team consists of a resident or specialist in emergency medicine, two nurses and one nursing assistant. When the patient is especially critical (for instance, cardiac arrest, level 1 trauma, upper airway obstruction), additional personnel (anaesthesiologists, surgeons, cardiologists, otorhinolaryngologists) supplement the resuscitation team.

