### EM: content and format

The EM consists of problem checklists, diagnosis checklists, procedure checklists and fact sheets in digital form. The checklists and fact sheets are accessed through a tablet computer located at each of the three resuscitation sections in the RR and displayed on a large screen visible to all members of the resuscitation team. Problem checklists consist of lists of interventions and diagnoses to consider based on the patient’s presenting symptoms. The popover windows display key clinical features suggestive of specific diagnoses. Diagnosis checklists consist of lists of interventions to consider during the management of a suspected diagnosis. Each intervention is associated with a popover window displaying indications, contraindications or risks associated with the intervention, and details regarding how the intervention is performed, as described in a previous study.^22^ Procedure checklists provide step-by-step guidance for the performance of key procedures as well as pictures. Fact sheets provide information such as medical dosages for sedation and anaesthesia for patients of all ages.

The collection of checklists and fact sheets covers the majority of symptoms, diagnoses and situations that may present in the RR, in accordance with the current European Core Curriculum in Emergency Medicine.^34^ The format and design of each checklist or fact sheet is informed by the literature pertaining to emergency and abnormal checklists in the aviation industry,^35–37^ articles on medical checklists^6 38–40^ and a selection of EMs.^41–44^ The content is customised to local circumstances in Lund’s ED (available medications, medication locations, local routines and phone numbers). EM content and format are further developed through iterative, rapid-cycle simulation-based testing and review by specialists, residents, nurses and nursing assistants who work clinically in Lund’s RR. Internet access to the EM is provided to the ED personnel prior to and during the study to allow for familiarisation and suggestions for improvement. Each checklist and fact sheet is approved by at least one specialist in emergency medicine and one nurse, both of whom work clinically in Lund’s RR.

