### EM: protocol for use

EM use during priority 1 management is strongly advocated but not mandatory. The documenting nurse is assigned the specific task of activating the digital EM. Regarding problem and diagnosis checklists, Do-Confirm is the default mode of EM use—the team first manages priority 1 patients without support from the EM. Once the management plan is finalised (a juncture which may be verbally confirmed with the team leader), the documenting nurse then asks the team: “Which checklist should I display?” When a checklist is displayed, the documenting nurse reads aloud each potential intervention or diagnosis for team consideration. The documenting nurse registers on the digital checklist whether each intervention is

Deemed indicated and has already been carried out.Deemed irrelevant or contraindicated.Deemed indicated and will be carried out thanks to EM use.

The physician responsible for patient management has the mandate to request that the EM not be used, to pause or terminate EM use at any time, and to depart from the recommendations featuring on the checklist. Physicians may also request that the EM be displayed directly and used in Read-Do mode or for retrieval of specific information (Sampling mode). Regarding procedure checklists and fact sheets, the default modes of use are Read-Do and Sampling, respectively. After EM use, teams grade the usefulness of the EM on a 1–6 Likert scale prior to logging out. If the documenting nurse logs in to the EM but the EM is not used, the nurse selects among potential reasons for non-use prior to logging out. Teams can also electronically request contact with the investigators to report specific events related to EM use.

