## Strengths, limitations and significance

The literature on medical crisis checklists argues that specific checklists, used according to clear protocols within specific contexts, improve performance. Yet there are no published data on how the introduction of an EM affects the performance of resuscitation teams during the management of actual priority 1 patients in the ED. The main strength of this study is that it evaluates EM use during the management of consecutive, unselected priority 1 patients by resuscitation teams in the ED.

In this study, some of the data on patient characteristics (such as age, chief complaint) and EM use (duration of use, checklists and fact sheets displayed) are automatically registered. Other EM use data (for instance, subjective team evaluation of the EM value, modality of EM use) are actively registered by the documenting nurse. The study is not a randomised controlled trial of EM use, and whether the EM is used or not is at the discretion of each resuscitation team. While these study aspects limit the evaluation of how routine EM use would impact on performance, the study will provide information about the circumstances under which resuscitation teams voluntarily use the EM and deem that it adds value to clinical practice. The study stretches over a 6-month period, allowing for an analysis of how resuscitation teams integrate a new tool within their clinical practice over time.

The study is not powered nor designed to detect causal relationship between EM use and patient outcome. The study will determine whether interventions carried out thanks to checklist use are indicated, of neutral relevance or not indicated based on the clinical context, as assessed by external reviewers. A limitation of this assessment stems from the fact that the external review is based on information available from patient records, which may not convey all the relevant factors affecting clinical decisions.

This study will be conducted in a single academic Swedish ED, limiting the external validity of the results. Yet this study will provide valuable information to guide the development of a tool that has the potential to improve the management of critical patients, and pave the way to multicentre studies of EM use in the ED.

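### Crude user versus non-user comparison of resuscitation-room stay and mortality carries immortal-time bias, because default (Do-Confirm) use of the emergency manual starts only after the plan is final

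*Protocol article*

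**What the plan says.** The Data analysis section of the protocol article uses descriptive statistics to determine "whether EM use is associated with length of stay in the RR, length of hospital admission and mortality". It adds: "These analyses are hypothesis-generating and not intended to infer causality". The closing section on strengths and limitations says in the same vein: "The study is not powered nor designed to detect causal relationship between EM use and patient outcome". The grouping named is EM use. The sentence gives no time origin.

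The section on the protocol for EM use fixes when use begins. For problem and diagnosis checklists, "Do-Confirm is the default mode of EM use—the team first manages priority 1 patients without support from the EM". The nurse asks which checklist to show "Once the management plan is finalised". The same section lets the physician ask for the EM at once, in Read-Do or Sampling mode, and makes these the default modes for procedure checklists and fact sheets respectively. Use is voluntary throughout.

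The Data acquisition section records log-in and log-out times, mode of use, time in the RR, age, presenting complaint, vital signs, and 7-day and 30-day mortality.

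**The concern.** Exposure is defined by something that happens during the stay being measured. To count as a Do-Confirm user, a patient must be alive and in the RR until the team has settled its plan. Early deaths and early departures fall into the non-user group because no checklist was yet due, whatever the team would have done later. Grouping by eventual use therefore credits users with a stretch of time in which they could neither die nor leave.

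This differs from ordinary confounding. It would arise even if teams chose to use the EM at random, and the general warning against causal reading does not tell the reader about it. At stake is a pair of published figures (longer RR stay, lower mortality) that could appear with no EM effect at all and be taken as a signal worth pursuing. RR stay is also a natural place to look for the delay in management that the ethics section mentions as a hypothesised risk.

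**Working it through.** The plan states no figure for this analysis; its sample size calculation concerns the primary outcome. The documents give no distribution of RR stay, time to a final plan, rate of use or mortality. Every input below is therefore an assumption, and every calculation sets the EM effect to zero.

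**1. RR stay, fixed time to plan.** Assume log-normal stay with median 60 min and log SD σ = 0.7, so the mean is M = 60 × exp(0.7²/2) = 76.66 min. EM use is possible only if stay exceeds c; a share u of those patients become users. With d = ln(c/60)/σ:

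- P(stay > c) = Φ(−d)
- Mean stay in users = M × Φ(σ − d)/Φ(−d)
- Mean stay in non-users = (M − u × P × user mean)/(1 − u × P)

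| c | u | P(stay > c) | Users | Non-users | Difference |
|---|---|---|---|---|---|
| 20 min | 30% | 0.942 | 80.5 | 75.2 | 5.3 min |
| 20 min | 50% | 0.942 | 80.5 | 73.3 | 7.2 min |
| 30 min | 30% | 0.839 | 87.2 | 73.1 | 14.1 min |
| 30 min | 50% | 0.839 | 87.2 | 69.0 | 18.2 min |

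**2. Mortality.** Assume 30-day mortality of 8%, and that the share of patients using the EM is the same in later deaths and in survivors.

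- *20% of deaths before the plan is final* (early 1.6%, later 6.4%). At 30% use: users 0.3 × 0.064/(0.3 × 0.984) = 6.5%; non-users (0.016 + 0.7 × 0.064)/(1 − 0.2952) = 8.6%; risk ratio 0.75. At 50% use: 6.5% against 0.048/0.508 = 9.4%; risk ratio 0.69.
- *5% of deaths before the plan is final* (early 0.4%, later 7.6%). At 30% use: 7.63% against 8.16%, ratio 0.94. At 50% use: 7.63% against 8.37%, ratio 0.91.

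**3. Both outcomes together, with some use starting at arrival.** This is a simulation of 1,000,000 patients per setting. Stay is gamma with shape 2 and mean 60 or 120 min; time to plan is exponential with mean 15 or 30 min. Half of teams are willing to use the EM, 2% of patients are at risk of early death (mean time 30 min), and 5% die later. Ranges run over the four combinations of stay and plan time.

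| Use starting at arrival | RR stay, users minus non-users | Mortality, users minus non-users |
|---|---|---|
| None | +8.8 to +19.4 min | −1.0 to −1.4 points |
| Half | +4.5 to +9.6 min | −0.4 to −0.7 points |
| All | about 0 | about 0 |

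For example, with mean stay 120 min, plan at 30 min and no use at arrival, stay is 128.9 against 109.5 min and mortality 5.89% against 7.27%.

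**4. Confounding by severity.** Return to step 2 with 1.6% early deaths, 6.4% later deaths, and 30% use in the 92% who survive. If use among later deaths is 37.5%, users number 0.276 + 0.024 = 0.300 and their mortality is 0.024/0.300 = 8.0%; non-users have 0.056/0.700 = 8.0%, ratio 1.0. If it is 45%, users have 0.0288/0.3048 = 9.4% and non-users 0.0512/0.6952 = 7.4%, ratio 1.28.

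**5. Does a landmark remove the artefact?** Among patients still in the RR at time L, use up to L depends only on the team's willingness and on whether the plan was final by L. Under the null model neither is related to the remaining stay, so the expected difference is zero. Simulating the step 3 model with no use at arrival and L = 30 min gave mean remaining stay within 0.2 min between groups (for example 44.8 against 44.8 min) and mortality within 0.1 point in all four settings.

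**The case against.** The strongest reply is that the plan never claims a causal effect. The analysis is descriptive, is labelled hypothesis-generating, and concerns outcomes found in neither the primary nor the secondary objectives. Detail on comparators and adjustment may sit in a full protocol or analysis plan that is not shown. Most of this stands and sets the severity. It does not remove the point: the article itself fixes both the grouping (by EM use) and the default start of use (after the plan), and the bias follows from those two statements together.

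Four stronger readings are tempting but are not supported.

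- *The bias is guaranteed.* It is not. Read-Do and Sampling use may start directly, and the article suggests these modes may suit a true crisis best, so patients who die early can be users. Step 3 shows the artefact vanishing if all use begins at arrival.
- *Its direction is fixed for mortality.* Teams choose when to use the EM. If they use it more in sicker patients, the ratio can reach or exceed 1, as step 4 shows.
- *The pre-implementation period is a contaminated or out-of-season comparator for these outcomes.* The Data analysis section states no comparison by period. Staff web access and the educational campaign before launch are undated and serve familiarisation and training; clinical access begins only in September 2023. Six months either side of that date do fall in different seasons, but moving the window back a year would exchange season for a longer secular gap.
- *These figures will drive the decision on a multicentre study.* The dissemination plan says only that this depends on the study results, without naming which.

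**Conclusion.** The concern holds for Do-Confirm use: a crude comparison of users with non-users builds in immortal time, which by itself pushes users' RR stay up and their mortality down. For length of hospital admission a delay of minutes is likely negligible against a stay counted in days.

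The size cannot be settled from the documents. The illustrations span roughly 4 to 19 minutes of RR stay when at least half of use waits for the plan. For mortality, with all use waiting, they span risk ratios of about 0.69 to 0.94 before any confounding by severity. The mortality figure is especially sensitive to the assumed share of deaths before the plan is final. Severity is minor: the analysis is exploratory and the primary outcome is unaffected.

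**What to change.** Keep the analysis descriptive and change how use is classified.

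1. Report RR stay and mortality by mode of use (Do-Confirm, Read-Do, Sampling), and state that Do-Confirm use starts after the plan is final.
2. Compare from a landmark: take patients alive and still in the RR at a fixed time after arrival, classify them by EM use up to that time, and count stay and death from it. Alternatively, treat EM use as a time-dependent exposure that begins at the recorded log-in time.
3. Show the results adjusted for, or stratified by, age, presenting complaint and vital signs. The landmark deals with the timing artefact but not with teams choosing whom to use the EM on.

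The cost is a little more analysis work. Log-in time, mode and time in the RR are already to be recorded, so no new type of data is planned for; placing log-ins after arrival assumes that arrival times come with the RR stay data. The landmark comparison leaves out early deaths and departures, which should be counted and reported separately, and it classes patients whose EM use begins after the landmark as non-users. The time-dependent version avoids that last drawback.

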### Patient and public involvement

Patients or the public were not involved in the design of this study, nor will they be involved in its conduct or in the reporting and dissemination of our research.

## Ethics and dissemination

### Ethical and safety considerations

The published literature strongly supports the claim that checklists, used as cognitive aids and not as substitutes for sound clinical judgement, improve performance. Several authors have hypothesised that checklist use may lead to distraction, delays in proper management or wrong management if the wrong checklist is used.^23 45 46^ However, published studies have not substantiated these concerns. A simulation-based trial of crisis checklists in Lund’s ED did not find any delay in the initiation of patient treatment, and all but one of 15 dangerous or inappropriate interventions were carried out by teams without checklist access.^22^ One study reported that EMs caused distraction during a small proportion of perioperative crises without negatively impacting on patient care.^5^ According to the study protocol, the physician in charge of patient management has the mandate to terminate EM use at any time, and no constraints are imposed on how the EM is used. For these reasons, patient risk incurred from EM access is deemed minimal.

Priority 1 patients are as a rule severely impaired by an acute critical condition and not in a state where informed consent is possible or appropriate to obtain. Written information about EM use will be available in Lund’s RR and provided to patients and relatives on request. Posters informing patients and their relatives about the ongoing trial and how to request non-inclusion will be placed throughout the ED. Patient identification numbers are pseudonymised automatically and data stored on a computer within the hospital’s firewall and locked in a room.

No identifying features of the personnel composing the resuscitation teams are registered during the study, aside from the identity of the personnel logging into the digital EM. Names of personnel involved in the care of specific patients are not recorded during the structured interviews. In the study that evaluated checklists in simulated critical conditions in Lund’s RR, over 90% of the care staff stated that they would use the checklist in real crises.^22^ Specific reviews of patient management will be based on information available in the medical charts, with the understanding that these cannot convey all relevant factors affecting clinical decisions. No formal complaints or chart reviews will be triggered by the case reviews in this study. For these reasons, risks incurred to resuscitation team personnel from EM access are deemed minimal. The Swedish Ethical Review Authority has approved the study (Dnr 2022-01896-01).

### Dissemination plan

Results will be published in a peer-reviewed journal and abstracts submitted to national and international conferences. The simulation-based study of crisis checklists in four EDs in the Skåne Region reported that >90% of staff at all sites would welcome checklist access during clinical care.^22^ Depending on the study results, a multicentre study using customised EMs will be considered.

## Strengths, limitations and significance

The literature on medical crisis checklists argues that specific checklists, used according to clear protocols within specific contexts, improve performance. Yet there are no published data on how the introduction of an EM affects the performance of resuscitation teams during the management of actual priority 1 patients in the ED. The main strength of this study is that it evaluates EM use during the management of consecutive, unselected priority 1 patients by resuscitation teams in the ED.

In this study, some of the data on patient characteristics (such as age, chief complaint) and EM use (duration of use, checklists and fact sheets displayed) are automatically registered. Other EM use data (for instance, subjective team evaluation of the EM value, modality of EM use) are actively registered by the documenting nurse. The study is not a randomised controlled trial of EM use, and whether the EM is used or not is at the discretion of each resuscitation team. While these study aspects limit the evaluation of how routine EM use would impact on performance, the study will provide information about the circumstances under which resuscitation teams voluntarily use the EM and deem that it adds value to clinical practice. The study stretches over a 6-month period, allowing for an analysis of how resuscitation teams integrate a new tool within their clinical practice over time.

The study is not powered nor designed to detect causal relationship between EM use and patient outcome. The study will determine whether interventions carried out thanks to checklist use are indicated, of neutral relevance or not indicated based on the clinical context, as assessed by external reviewers. A limitation of this assessment stems from the fact that the external review is based on information available from patient records, which may not convey all the relevant factors affecting clinical decisions.

This study will be conducted in a single academic Swedish ED, limiting the external validity of the results. Yet this study will provide valuable information to guide the development of a tool that has the potential to improve the management of critical patients, and pave the way to multicentre studies of EM use in the ED.
